### Setting

2.2

In France, all patients over the age of 16 must follow a coordinated care pathway. General practitioners (GP) are at the center of this system. They coordinate access to care and specialists, are involved in screening and must be consulted as a priority. The GP system is based on a reciprocal choice: that of the patient and that of the GP.

The study is based on the regular GP/patient pair to measure the effect of the intervention. A cluster is defined as a group of GPs within the same primary practice address.

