### Randomization

2.5

GPs will be clustered within practices to avoid contamination bias stemming from shared tracking mechanisms and communication among GPs within a practice. As a result, two GPs working in a given practice will be assigned to the same study arm. The women will then be allocated to the same arm as their GP.

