##### Measure SMDM implementation and assess the level of decision-making conflict

2.8.2.2

The second secondary objective is to measure the effect of the intervention on SMDM implementation and quality, as part of an ancillary study. While the use of DAs is still marginal in occupational practices, the study should provide a better understanding of how such a tool is used and perceived when it is made available to healthcare professionals.

To assess the SMDM quality, a composite criterion will be used. The validated Shared Decision Making Questionnaire (SDM-Q-9) (38) will be used to evaluate SMDM implementation. The validated Decisional Conflict Scale (DCS) will be used to assess decision-making conflict (39). Intent to participate will be measured using a multiple-choice question. Knowledge about OS and women’s doubts, questions and concerns will be assessed and collected using a questionnaire created for the study. Secondary outcomes will be SDM-Q9 and DCS scores, intention to participate and level of knowledge. This will be measured 2 months after the intervention, in a sample of women from each study arm (see **Supplementary Material 1**).

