#### Exploratory secondary analyses

2.10.2

Participation rates in exploratory subgroup analyses will be studied in the same manner as the primary endpoint. The same margin of non-inferiority will be used. There is no provision for alpha risk adjustment for these analyses. The different subgroups are: (i) women aged 50 to 59/60 to 69/70 to 74 years at baseline, (ii) beneficiaries/not beneficiaries of the Complementary Solidarity Health at baseline, (iii) women who consulted/did not consult at least one GP, gynecologist or midwife (during the follow-up period for women who did not have a bilateral mammogram during the 18 months, or from baseline until the date of the bilateral mammogram for women who had the screening) (iv) women residing in a municipality with a low deprivation index (per quintile of the deprivation index) (41).

Predictors of OS use will be assessed using a multivariate generalized mixed model fitted to the physician as a random effect, and as fixed effects: (i) the number of visits to the treating physician, GP, gynecologist, or midwife in the 18 months prior to enrolment, and from baseline to bilateral mammography or to the end of the follow-up period for women who did not have bilateral mammography, (ii) the woman’s age at baseline, (iii) the presence of a chronic condition measured *via* chronic drug use and testing, (iv) previous participation in OS.

A stepwise algorithm based on the Akaike information criterion (AIC) will be implemented to select variables that provide meaningful information independent of the main factors.

SMDM quality will be measured using the DCS and SDM-Q9 scales, responses to participation intent and knowledge of women about the OS. It will be compared between groups using a Student superiority test.

The care pathway of the women responding to the questionnaires will be studied and in particular the concordance between patients’ intention and effective participation in BC screening.

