#### Ancillary study sample

2.11.2

In her article, Pérez-Lacasta observed a difference in the decision-making conflict scale score between women who received information and those who did not of 18.53 vs. 13.77 (standard deviation at 20.25) (43). On these assumptions, 762 responses would be required to arrive at a significant difference.

The ancillary survey conducted by questionnaire to assess SMDM quality will be carried out on an independent sample of 5,000 women, equally divided between the 2 arms. Based on a response rate of 20%, the number of questionnaires collected will be 1,000.

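### The Student test planned for the ancillary shared-decision outcomes ignores randomisation by practice, as does their sample size, and the multiple-choice intention item has no stated scoring; the expected effect is small

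*Protocol article*

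**What the plan says.** All references are to the protocol article.

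- **Randomisation (sections 2.2 and 2.5).** "A cluster is defined as a group of GPs within the same primary practice address". Practices are randomised as units: "The women will then be allocated to the same arm as their GP".
- **Ancillary outcomes (section 2.8.2.2).** "To assess the SMDM quality, a composite criterion will be used". The same section then lists separate outcomes: "Secondary outcomes will be SDM-Q9 and DCS scores, intention to participate and level of knowledge". On intention it says: "Intent to participate will be measured using a multiple-choice question". The women are sampled from each trial arm.
- **Ancillary analysis (section 2.10.2).** "SMDM quality will be measured using the DCS and SDM-Q9 scales, responses to participation intent and knowledge of women about the OS". The next sentence reads: "It will be compared between groups using a Student superiority test". No practice term is mentioned.
- **Ancillary size (section 2.11.2).** From a difference of 18.53 versus 13.77 and a standard deviation of 20.25: "On these assumptions, 762 responses would be required to arrive at a significant difference". The plan mails 5,000 women, half per arm, and expects a 20% response, so 1,000 questionnaires. Neither power nor a design effect is given.
- **Elsewhere.** The primary analysis has a practice random effect (2.10.1), the predictor model has a physician random effect (2.10.2), and the main sample is multiplied by 3.35 for clustering (2.11.1).

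**The concern.** The woman's arm is fixed by her practice, and the intervention works partly through the GP, who receives a letter on the stages of shared decision-making and an incentive to apply them. Answers about shared decision-making from women of the same practice are therefore likely to be correlated. A two-sample Student test assumes they are not, so its standard error is too small whenever that correlation is positive. The article allows for clustering in its other two models and in its main sample size, but neither in this comparison nor in the number behind it.

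Separately, the one named test appears to cover a multiple-choice answer. A mean of unscored categories has no meaning.

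At stake is the second secondary objective. If participation turns out to be merely non-inferior, evidence of better decisions becomes the main positive argument for the decision aid; section 3.1 names reduced decisional conflict as an expected gain.

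**Working it through.** **Inputs.** Difference 18.53 − 13.77 = 4.76, SD 20.25, 762 responses required, 5,000 mailed, 20% response, 1,000 returned (section 2.11.2). Two-sided 5% (section 2.10). ICC 0.05, 48 women per practice, 1,570 practices (section 2.11.1). The ICC is given for participation in the main study; its use for decisional conflict is my assumption, so a range is shown.

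**1. Reproduce 762.** For independent women, n per arm = 2(z₀.₉₇₅ + z_power)² (SD/difference)².

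- 90% power: 2 × (1.960 + 1.2816)² × (20.25/4.76)² = 380.3, rounded up to 381 per arm, **762 in total**: an exact match.
- 80% power: 285 per arm, 570 in total.
- One-sided 5% at 95% power gives 784, which is close but contradicts the stated two-sided level.

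So 762 is an individually randomised figure with a design effect of 1. The 90% is inferred, not stated.

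**2. Design effect if responders are spread over all practices.** DE = 1 + (m − 1) × ICC, where m is the response-weighted mean number of responders per practice. With 1,000 responders falling at random on 1,570 equal-sized practices (1,000/1,570 = 0.637 each), m = 1 + 0.637 = 1.637.

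- DE = 1 + 0.637 × 0.05 = 1.032.
- Standard error understated by a factor √1.032 = 1.016.
- True error of the unadjusted test = 2[1 − Φ(1.96/√1.032)] = 5.4%.
- Required number = 2 × ⌈381 × 1.032⌉ = 788.
- For ICC 0.01 to 0.10: DE 1.01 to 1.06, error 5.1% to 5.7%, required number 768 to 812.

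**3. If responders are more concentrated (ICC 0.05).** Power is for a practice-adjusted test with 1,000 responses.

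| m | DE | True error, Student test | Required N | Power |
|---|---|---|---|---|
| 1.64 | 1.03 | 5.4% | 788 | 95.5% |
| 3 | 1.10 | 6.2% | 840 | 94.3% |
| 5 | 1.20 | 7.4% | 916 | 92.4% |
| 10 | 1.45 | 10.4% | 1,106 | 87.0% |

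**4. How realistic is the last row?** Ten responders at a 20% response need 10/0.20 = 50 women mailed per practice, against an average of 48 eligible. The 5,000 letters would go to 5,000/50 = 100 practices, with practically every eligible woman in them mailed. It is an extreme bound.

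**5. How much clustering do 1,000 responses absorb?** 1,000/762 = 1.31. At ICC 0.05 this corresponds to m = 1 + 0.31/0.05, about 7 responders per practice.

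**6. Intention.** Section 2.8.2.2 makes it a multiple-choice question and a separate outcome. Section 2.10.2 counts it among the measures of decision quality and names one test of means. Section 2.8.2.2 also mentions a composite criterion, but the article neither builds one nor scores the item, and the sample size rests on the decisional conflict score alone.

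**The case against.** Four points can be made for the plan.

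- **The ancillary sample is described as independent.** This does not help: the women are still divided between arms that were set by practice.
- **The inflation is slight under the natural reading of the sampling.** This stands. Nothing in the article suggests that the 5,000 women come from a few practices. A reader might infer that the false-positive rate is about doubled, at 10.4%, or that the ancillary study is underpowered. The documents support neither: the first needs the extreme concentration in step 4, and 1,000 responses exceed the 788 needed under wide spread. Even at the extreme, an adjusted test keeps 87% power.
- **A Student test on intention may be legitimate.** A reader might infer that the test is simply wrong for this outcome. That goes too far. The singular subject of the test sentence may refer to the composite, and the supplementary material, which is not shown, may score the item. What stands is that the article lists intention separately and leaves both the scoring and the object of the test unclear. A composite score would still need a practice adjustment.
- **The analyses are ancillary and sit under an exploratory heading.** This stands and limits the weight of the point.

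It is no answer that such detail belongs in a statistical analysis plan: the article does name a test, and that test does not match the design.

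**Conclusion.** The point holds as a minor inconsistency. The named test and the 762 both treat women as independent in a trial randomised by practice, while the primary analysis does not. The direction of the error is certain if the within-practice correlation is positive; its size depends on responders per practice, which the article does not give. The best estimate is a true error of about 5.4% instead of 5%, with about 788 responses needed. It rests on three assumptions: the participation ICC carries over to decisional conflict, practices are of equal size, and responders are spread at random over all 1,570. The fault is the omitted adjustment, not a demonstrated loss of power. For intention, a comparison of means is unsuitable unless the item is scored or enters a defined composite. Only secondary and ancillary results are affected.

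**What to change.** - **Section 2.10.2, scores.** Compare the Decisional Conflict Scale, SDM-Q9 and the knowledge score with a linear model that accounts for practice, by a random practice effect or cluster-robust standard errors. With many practices supplying one response or none, the practice variance may be poorly estimated, so the robust option is a sound alternative.
- **Section 2.10.2, intention.** Use a logistic, ordinal or multinomial model, according to the response options, with the same adjustment. If a composite is meant, define it and its scoring, and say which quantity is tested.
- **Section 2.11.2.** State the power behind 762 (90% reproduces it, but the sponsor should confirm), the ICC assumed for decisional conflict, the expected responders per practice and the resulting design effect. Say that the 5,000 women are drawn across practices, if that is so.

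The cost is wording. No more questionnaires are needed if the sample is spread across practices; at the extreme of 10 responders per practice, keeping 90% power would take 1,106 responses.

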#### Analysis population

2.10.3

Statistical analyses will be performed on all randomized physicians and patients included in the study. As data are collected on medico-administrative databases, very little missing data is expected (only the very rare case of women changing reimbursement schemes). If these women did not have a mammogram as part of the OS at the time of their change of plan affiliation, they will be considered non-participants for the assessment of the primary endpoint in the ITT analysis. Women who died during the study period and had not had a mammogram at the time of death, will also be considered non-participants for the assessment of the primary endpoint. The same applies to women who underwent individual screening during the study period.

A sensitivity analysis on a Per-Protocol population will be performed by removing from the analysis patients for whom a return mail has been received (for example “No longer living at the address indicated”)), patients who have moved outside the Pays de la Loire region, patients who have changed regular GP, patients whose regular GP has ceased to practice during the study period or has died, patients who have been individually screened, who do not enter OS for known medical reasons after the start of the study, or who died during the follow-up period.

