#### Main criterion

2.10.1

The percentage of women having undergone BC screening, 18 months after the intervention, will be compared between the arms using a generalized linear mixed model, to adjust the analysis for the random effect of the practice.

A two-sided 95% confidence interval of the difference in participation rates between the two arms will be calculated. The lower bound of this confidence interval will be compared to the non-inferiority margin. Non-inferiority will be demonstrated if the lower bound of the confidence interval is greater than the margin of non-inferiority defined at 2%, on the Intention to Treat (ITT) population and Per-Protocol population. If non-inferiority is demonstrated and if the participation rate in the intervention arm is higher than the participation rate in the control arm, the hypothesis will be verified with a superiority test (bilateral at 5%, according to the same model as that of the non-inferiority analysis) (40). If the test is significant, it will be concluded that the participation rate in the intervention arm is significantly higher than the participation rate in the control arm.

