#### Main study sample

2.11.1

Based on a participation rate in 2020 of 49% for the five participating departments (11) assuming a margin of non-inferiority of 2 points to demonstrate that participation is non-inferior in the intervention arm, and considering a power of 80% and a bilateral alpha risk of 5%, the number of women to be included is equal to 9,808 in each arm, being a total of 19,616 women.

There are 2,847 GPs in the five departments (42). Considering that GPs operate from 1,570 different practices (42) the number of women targeted per practice will be 48. With an average cluster size of 48 women and an intraclass coefficient of 5%, the number of subjects to be included to account for this cluster randomization must be multiplied by 3.35, or 65,647 women (32,824 per group).

The number of GPs included will be approximately 2,847 in the five departments. The recruitment potential is approximately 25,000 women per month (personal communication from the CRCDC). The inclusion will therefore be done over 3 consecutive months.

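### The per-protocol set is a condition for non-inferiority in 2.10.1 but a sensitivity analysis in 2.10.3, and it removes women for a post-randomisation event that is itself a failure of the endpoint

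*Protocol article*

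**What the plan says.** The primary outcome (2.8.1) is participation in organised breast cancer screening (OS) within 18 months of the invitation.

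- **Decision rule (2.10.1, Main criterion).** The lower bound of the two-sided 95% confidence interval must clear the 2-point margin "on the Intention to Treat (ITT) population and Per-Protocol population".
- **Label (2.10.3, Analysis population).** The same analysis is introduced differently: "A sensitivity analysis on a Per-Protocol population will be performed by removing from the analysis".
- **ITT handling (2.10.3).** After ruling that women who die without a mammogram count as non-participants, the text adds: "The same applies to women who underwent individual screening during the study period".
- **Per-protocol handling (2.10.3).** The removed groups include "patients who have been individually screened, who do not enter OS for known medical reasons after the start of the study". Women with returned mail, a move out of the region, a change or loss of regular GP, or death are also removed.
- **Intervention (2.6).** Women in the intervention arm get a flyer that mentions the decision aid and urges them to see their GP for a shared decision. GPs get a matching letter.

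**The concern.** There are two linked problems.

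**Role.** If ITT passes and per-protocol fails, 2.10.1 says non-inferiority is not shown, whereas a sensitivity analysis would normally leave the ITT conclusion standing. The confirmatory rule should not allow two readings.

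**Content.** A woman screened individually has not, on that account, departed from her allocated arm. She could have been sent and have read exactly the letter she was meant to get. What she did is an alternative to the endpoint event, and ITT scores it as a failure. A woman who does not enter OS for a medical reason that emerges later is likewise a non-event. Removing both groups changes the estimate from OS participants over all women to OS participants over women who did not fail in these particular ways. Since the intervention prompts consultation and deliberation, the number removed could differ by arm, and randomisation no longer protects the comparison.

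With a margin of only 2 points, a modest imbalance in the removed share could matter for a test that 2.10.1 makes decisive.

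**Working it through.** **Inputs from the article (2.11.1, Main study sample).** OS rate 49%, margin 2 points, power 80%, two-sided alpha 5%, 9,808 women per arm before clustering, cluster size 48, intraclass coefficient 0.05, design effect 3.35, 32,824 per group after inflation.

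**Not in the article.** The share of women removed for individual screening or later medical reasons, overall or by arm. *Assumption:* 0–15% in control, with an arm difference of 0–3 points.

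**Step 1. Reproduce the plan's figure.** n per arm = (1.96 + 0.8416)² × 2 × 0.49 × 0.51 / 0.02² ≈ 9,807.2, rounded up to 9,808, as stated. Design effect = 1 + 47 × 0.05 = 3.35. 19,616 × 3.35 = 65,714 against the stated 65,647, a 0.1% difference. At 32,824 per group, SE = √(2 × 0.49 × 0.51 × 3.35 / 32,824) = 0.00714, and power = Φ(0.02/0.00714 − 1.96) ≈ 80%.

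**Step 2. Effect of the exclusion.** Let p be the OS rate among all women and s the share removed, all of them non-participants. The ITT rate is p and the per-protocol rate is p/(1 − s).

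**Step 3. Equal OS rates (49% in both arms, ITT difference 0), more women removed in the intervention arm.**

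| Arm difference in s | Shift, control s = 0% | Control s = 5% | Control s = 10% | Control s = 15% |
|---|---|---|---|---|
| 0 points | 0 | 0 | 0 | 0 |
| 1 point | +0.49 | +0.55 | +0.61 | +0.69 |
| 2 points | +1.00 | +1.11 | +1.24 | +1.39 |
| 3 points | +1.52 | +1.68 | +1.88 | +2.11 |

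Example: 0.49/0.87 − 0.49/0.90 = 56.32% − 54.44% = +1.88 points.

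**Step 4. Direct switch of 2 points from OS to individual screening, control s = 10%.** ITT difference = 47 − 49 = −2.00. Per-protocol difference = 0.47/0.88 − 0.49/0.90 = 53.41% − 54.44% = −1.04. About half of the deficit disappears, and the result hardly depends on the control share (−1.02 to −1.04 over 0–15%). At this point the ITT test passes 2.5% of the time by construction. The per-protocol test alone passes about 25–27% of the time.

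**Step 5. Equal OS rates, individual screening 2 points lower in the intervention arm (8% against 10%).** ITT difference = 0. Per-protocol difference = 0.49/0.92 − 0.49/0.90 = 53.26% − 54.44% = −1.18. With 3.35 kept as the design effect, SE = √[3.35 × (0.5444 × 0.4556/29,542 + 0.5326 × 0.4674/30,198)] = 0.00747. P(pass) = Φ((0.02 − 0.0118)/0.00747 − 1.96) ≈ 19%. The planned power on the full set is about 80%. Merely losing 10% of women equally in both arms gives SE 0.00750 and about 76%, so nearly all of the fall comes from the arm difference.

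**Step 6. Joint rule.** If both sets must pass, P(both pass) ≤ P(ITT passes). If per-protocol is only a sensitivity analysis, ITT decides alone. Either way, the probability of false non-inferiority is no higher than that of ITT alone.

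**The case against.** **The size depends on undocumented rates.** This stands. With equal removed shares the shift is zero. A reader might infer that the exclusion moves the result by almost the whole margin. That needs an arm difference of about 3 points (for instance 10% against 13%), and nothing in the article supports an effect of that size from a flyer and a letter. The figures above are a conditional range, not a forecast.

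**The exclusion cannot produce a false claim.** This also stands. A reader might infer that the per-protocol set could hide a real loss of OS participation and let non-inferiority through. It could not, because ITT must pass under either reading. What remains is a second test that protects less than it appears to, or one that blocks a valid claim.

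**The blocking case is narrow.** In Step 5 total screening falls from 59% to 57%, so a warning might be welcome. However, the endpoint in 2.8.1 is OS participation only, and the ITT difference on it is zero.

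**The contradiction is mostly a label.** 2.10.1 holds the only explicit success rule and 2.10.3 states no competing one. This is fair, and it makes the repair easy. But the label still gives a sponsor grounds to set aside a per-protocol failure.

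**Medical non-entrants have a rationale.** Table 1 already bars women under follow-up or surveillance, so dropping those who later qualify keeps the set to women still eligible for OS. The selection concern is weaker here than for individual screening. It does not vanish, because such reasons may come to light at the consultation that the intervention encourages.

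**Conclusion.** The point holds as a should-fix. Two structural facts need no assumption. The per-protocol analysis has two roles in the text, and its exclusions include women who are non-participants for the endpoint because of something that happened after randomisation. For individually screened women the ITT rule says so explicitly.

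The size is conditional. With 49% OS in both arms and 0–15% of control women removed, the per-protocol difference is displaced by 0 to about 2.1 points as the arm difference in removed share goes from 0 to 3 points. A 2-point switch out of OS shows as about −1.0 instead of −2.0. Two points less individual screening than a 10% control cuts the chance of passing per-protocol to about 19%, against planned power of about 80%.

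The ITT analysis and its error rate are intact. The plan is exposed to an ambiguous conclusion, and to a second test that is either a poor safeguard or an unwarranted obstacle.

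**What to change.** 1. State one role for the per-protocol analysis, in the same words, in 2.10.1 and 2.10.3: either a condition for the non-inferiority claim or a sensitivity analysis. If it is a condition, say that a per-protocol failure means non-inferiority is not shown.
2. In 2.10.3, keep individually screened women and those who do not enter OS for later medical reasons in the per-protocol denominator as non-participants, as in ITT. The shift from these exclusions is then zero.
3. Base per-protocol exclusions on failure to receive the allocated mailing, such as returned mail. Review the remaining exclusions (moves, change or loss of GP, death) on the same principle. They also arise after randomisation and can follow a letter that was delivered, so they should not be treated as delivery failures without argument.
4. Optional: a supportive ITT analysis of any screening mammogram, organised or individual, which would show directly whether women moved between the two routes.

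The cost is wording in two sections, settled before outcome data by arm are seen. Item 4 adds one model run. The individual-screening data must already be identified to apply the existing rules.
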